## 9. STUDY PROCEDURES

Prospective participants may be pre-screened by telephone: the study will be explained, the inclusion and exclusion criteria reviewed, volunteers' questions answered, and Visit 1 scheduled. Each woman will be seen in approximately 8 or 9 visits (depending on randomization) and have one scheduled follow-up call/contact.

### 9.1. Visit 1: Screening/Enrollment

Visit 1 should be scheduled at a time when the volunteer does not expect to be menstruating. Volunteers will be consented at Visit 1 and undergo procedures to confirm they are eligible to continue in the study.

- The study and informed consent form will be reviewed and all volunteer questions will be answered. If the volunteer wishes to participate and meets preliminary study criteria, she will be asked to review and sign an informed consent form. The Principal Investigator (PI) or designee will sign the form and provide a copy to the participant. Permission will be requested as part of the informed consent process for storage of the biologic samples obtained during the study for results confirmation and/or possible future testing will be explained, as allowed by the site.
- An interview will be conducted to obtain medical history and demographic information.
- Height, weight, and blood pressure will be measured.
- Directed physical exam will be performed if history is significant for medical condition.
- A urine specimen will be obtained for a urine pregnancy test to confirm that the participant is not pregnant and to perform a dipstick urinalysis if symptomatic for infection (specimen will be clean-catch if the participant is symptomatic, and urine microscopy and culture will be performed as clinically indicated).
- An HIV test will be performed, along with appropriate counseling and/or referral.
- Blood samples will be collected for CBC, serum chemistries, fasting lipids, and HBsAg testing.
- A pelvic examination (including bimanual examination) will be performed with findings managed as outlined in [Table 12: Safety Management Plan for Local Toxicity](#) and below:
  - Sample for wet mount will be taken during the pelvic exam if the participant is symptomatic for vulvovaginal candidiasis or BV
  - Sample for *Trichomonas vaginalis* will be taken
  - Gram stain and pH will be performed at the site to assess for BV
  - Specimens for GC and CT will be collected
  - A Pap smear will be performed, as consistent with current practice guidelines
- Symptomatic urinary tract infection (UTI) and yeast infections will be treated, preferably with oral medication. If symptomatic trichomoniasis or BV is diagnosed, the participant will be treated and will not be allowed to continue in the study.

- The participant will be instructed to abstain from vaginal intercourse starting after Visit 1 through the sixth day after the last study visit. (Women who are sterilized or who have a sterilized partner must abstain from vaginal intercourse starting 48 hours before Visit 3 through the sixth day after the last study visit.)

There should be sufficient time between Visit 1 and Visit 2 to allow any needed lab results to become available. If any tests reveal that the participant does not meet inclusion/exclusion criteria, the participant will not continue to Visit 2. If more than eight weeks pass between Visit 1 and Visit 2, then Visit 1 procedures must be repeated, as described in the study manual.

## 9.2. Visit 2: Confirmation of Ovulation

Visit 2 will be scheduled for day 21 (+/- 1 day) of the participant's menstrual cycle to confirm ovulation.

- An interval medical history will be collected.
- Eligibility criteria will be reviewed. If any lab tests reveal that the participant is no longer eligible, the visit should not proceed and the participant will not continue in the study.
- The study staff will ask the participant if she followed the instructions regarding vaginal intercourse. If she did not, she will be reminded of protocol requirements.
- A directed physical exam, dipstick urinalysis (and possibly microscopy/cultures) and/or wet mount/pH will be performed, if indicated. If a symptomatic yeast or UTI infection is diagnosed, the participant will be treated and Visit 2 will be rescheduled for the next menstrual cycle. If symptomatic trichomoniasis or BV is diagnosed, the participant will be treated and will not be allowed to continue in the study.
- A urine specimen will be obtained for a urine pregnancy test.
- Blood will be drawn for P4 level.
- The participant will be instructed to abstain from all other vaginal activity starting 48 hours before Visit 3 until the sixth day after the last study visit. This includes:
  - Anal sex, receiving oral sex, digital vaginal stimulation, and use of sex toys;
  - Use of any vaginal product other than the study product including tampons, spermicides, lubricants, and douches (for intermenstrual spotting or bleeding, unscented menstrual pads but not tampons may be used); and
  - Any other vaginal activity.
- The participant will be reminded to abstain from all vaginal intercourse through the sixth day after the last study visit. (Women who are sterilized or who have a sterilized partner must abstain from vaginal intercourse starting 48 hours before Visit 3 through the sixth day after the last study visit.)

If ovulation is not confirmed at Visit 2 by a P4 of  $\geq 3$  ng/ml, Visit 2 will be repeated in the same menstrual cycle; repeat Visit 2 will be scheduled on day 23 (+/- 1 day) of the participant's menstrual cycle and a urine pregnancy test will not be required. If ovulation is not confirmed at repeat Visit 2, the participant is not eligible to continue in the study.

If ovulation is confirmed at Visit 2 or repeat Visit 2 by a P4 of  $\geq 3$  ng/ml, Visit 3 will be scheduled on or before day 24 (but not later than day 26) of the participant's menstrual cycle. If results are available and ovulation is confirmed, and the participant confirms she has not engaged in any vaginal activity or used any vaginal products in the prior 48 hours, Visit 3 may occur on the same day as Visit 2.

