## **7. INVESTIGATIONAL PLAN**

### **7.1. Overall Study Design**

This will be an outpatient, randomized, partially blinded, placebo-controlled, parallel study. Eligible participants will be randomized in a 2:2:1 ratio (TFV/LNG:TFV-only:placebo) to use 1 of the 3 IVRs for approximately one month.

All women will undergo a screening visit to detect the presence of exclusion factors. Blood will be drawn for P4 at Visit 2, scheduled on Day 21 of the participant's menstrual cycle, to confirm ovulation in the control cycle. Ovulation will be considered confirmed by a P4 level of  $\geq 3.0$  ng/ml. Once ovulation is confirmed, participants will undergo baseline sampling at Visit 3.

Participants will initiate use of the IVR in the clinic on day 7 of their next menstrual cycle (Visit 4). Participants will undergo colposcopy and collection of blood and genital samples for safety, PK, and PD before IVR insertion. After observed IVR insertion, assessment of PK in blood will be done at 1, 2, 4, and 8 hours for all participants and in CVF at a randomly selected time point 1, 2, 4, or 8 hours (Visit 4 post-insertion).

Visit 5 will take place 24 hours after insertion and will include assessment of PK in blood, CVF, and tissue. Colposcopy will be performed.

Starting on day 10 of their cycle, participants will use an ovulation predictor kit to determine the day of ovulation, at which point their cervical mucus will be assessed for PK and PD (Visit 6). They will undergo colposcopy and collection of blood and CVF for PK.

Visit 7 will occur 8-10 days after Visit 6. Participants will complete an acceptability questionnaire, undergo colposcopy and collection of blood and genital samples for safety, PK, and PD. The IVR will be removed prior to genital biopsies. Visit 8 will take place 24 hours after IVR removal, and will include assessment of PK in blood and cervicovaginal fluid, and PK in cervical mucus.

Assessment of PK in tissue after IVR removal will occur at a randomly selected time point (24 hours [Visit 8] or 72 hours [Visit 9]).

The site will contact the participant 1-2 weeks after final genital sampling to ask about AEs experienced and medications taken since the last visit. The participant will then be exited from the study, unless she has symptoms that require follow-up. There will be approximately 8 or 9 visits and one scheduled follow-up call/contact over approximately 2½ months.

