### 8.1. Inclusion Criteria

Volunteers must meet all of the following criteria prior to genital sampling at Visit 3.

- Age 18-45 years, inclusive
- General good health (by volunteer history and per investigator discretion) without any clinically significant systemic disease (including, but not limited to significant liver disease/hepatitis, gastrointestinal disease, kidney disease, thyroid disease, osteoporosis or bone disease, and diabetes)
- Currently having regular menstrual cycles of 26-35 days by participant report
- History of Pap smears and follow-up consistent with standard medical practice as outlined in the study manual or willing to undergo a Pap smear
- Protected from pregnancy by one of the following:
  - Sterilization of either partner. *Note: Women protected from pregnancy by sterilization of either partner must abstain from vaginal intercourse from 48 hours prior to Visit 3 until the sixth day after the last study visit.*
  - Willing to abstain from vaginal intercourse from Visit 1 until the sixth day after the last study visit.
- Willing to abstain from any other vaginal activity and the use of vaginal product other than the study product including tampons, spermicides, lubricants, and douches starting 48 hours before Visit 3 until the sixth day after the last study visit
- Vaginal and cervical anatomy that, in the opinion of the investigator, lends itself to easy colposcopy and genital tract sample collection
- Negative urine pregnancy test
- $P4 \geq 3$  ng/ml

- Willing to give voluntary consent, sign an informed consent form and comply with study procedures as required by the protocol

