### 9.3. Visit 3: Baseline Sample Collection

Once it has been confirmed that the participant meets all of the inclusion criteria and none of the exclusion criteria, baseline blood and genital tract samples will be taken at Visit 3. The visit should be scheduled on or before day 24 (but not later than day 26) of the same menstrual cycle in which ovulation was confirmed.

- An interval medical history will be collected.
- The study staff will ask the participant if she followed the instructions regarding vaginal products and vaginal activity. If she did not, she will be reminded of protocol requirements. Visit 2 and 3 may be rescheduled for her next menstrual cycle at the investigator's discretion.
- A directed physical exam, dipstick urinalysis (and possibly microscopy/cultures) and/or wet mount/pH will be performed, if indicated. If a symptomatic yeast or UTI infection is diagnosed, the participant will be treated and Visits 2 and 3 will be rescheduled for the next menstrual cycle. If symptomatic trichomoniasis or BV is diagnosed, the participant will be treated and discontinued.
- A urine specimen will be obtained for a urine pregnancy test.

If the participant meets all eligibility criteria and agrees to participate, she will continue in the study.

- A pelvic exam will be performed and the following procedures will be completed in the order listed. Findings will be managed as outlined in [Table 12: Safety Management Plan for Local Toxicity](#).
  - Transvaginal ultrasound to assess endometrial thickness.
  - Collection and processing of one endometrial biopsy (EVMS site only) for LNG PD as outlined in the study manual.
  - Collection and processing of cervicovaginal biopsies for safety (one at Profamilia and two at EVMS) and TFV PD (one biopsy at EVMS) as outlined in the study manual.
  - Applicable post-biopsy instructions will be discussed with the participant.
- A participant guidebook (which will include instructions regarding post-biopsy care, vaginal restrictions, and visit information) will be given to the participant to record any medications she takes or symptoms she experiences for the duration of the study, sexual and vaginal activity, removal/expulsion and reinsertion of study product, as well as menses and intermenstrual spotting. She will be instructed to bring the guidebook to every visit.
- The participant will be instructed to contact the site at any time during the study if she experiences:
  - Fever

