## 9.7. Visit 7: IVR Removal and Sample Collection

Visit 7 should occur 8-10 days after Visit 6 (or repeat Visit 6) to allow for the maximum number of days of IVR use in this menstrual cycle while ensuring that participants are seen for final genital sampling before their next menses begins.

- The guidebook, including reported AEs, CTs and the menses diary, will be reviewed.
- The study staff will ask the participant if she followed the instructions regarding vaginal products and vaginal activity. If she did not, she will be reminded of protocol requirements and the visit will continue.
- The participant will complete an acceptability questionnaire.
- A urine specimen will be obtained for a urine pregnancy test.
- A directed physical exam, dipstick urinalysis (and possibly microscopy/cultures) and/or wet mount/pH will be performed, if indicated. If a symptomatic infection is diagnosed, study procedures will continue per investigator discretion and the participant will be treated after completion of the visit procedures.
- Blood will be drawn for TFV and TFV-DP PK, LNG/SHBG PK/PD, CBC, serum chemistry, fasting lipids, and P4.
- A pelvic exam will be performed and the following procedures will be completed in the order listed. Findings will be managed as outlined in [Table 12: Safety Management Plan for Local Toxicity](#).
  - The biopsy sites from previous sampling will be assessed. Subsequent procedures will be done at the investigator's discretion.
  - Collection of vaginal aspirate for TFV PK.
  - Preparation of vaginal swabs for TFV PK, TFV PD, to test for microflora, and semen biomarkers as outlined in the study manual.
  - Collection of CVL for safety and TFV PD.
  - Naked eye/colposcopic examination.
  - Collection of cervical mucus for LNG PK.
  - Transvaginal ultrasound to assess endometrial thickness.
  - The IVR will be removed.
  - Collection and processing of one endometrial biopsy (EVMS only) for LNG PD as outlined in the study manual.
  - Collection and processing of up to three biopsies (up to five at EVMS) for safety and TFV and TFV-DP PK, as outlined in the study manual.
  - Appropriate post-biopsy instructions will be discussed with the participant.
- Post-removal ring procedures will be immediately carried out as outlined in the study manual.
- The participant will be given applicable reminders as described in Visit 4.

- Visit 8 will be scheduled to allow for sample collection 24 hours after IVR removal.

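### Control-cycle progesterone tests and Visit 3 tissue use fixed cycle days built on about 28 days, although 26-35 day cycles are eligible and Visit 7 is timed from ovulation; the longest eligible cycles do not fit

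*Protocol*

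**What the plan says.** **Eligibility.** Section 8.1 requires "Currently having regular menstrual cycles of 26-35 days by participant report".

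**Control cycle: fixed days.** Section 9.2: "Visit 2 will be scheduled for day 21 (+/- 1 day) of the" cycle, to confirm ovulation. If P4 is low, "repeat Visit 2 will be scheduled on day 23 (+/- 1 day) of the participant's menstrual cycle". In Section 7.1, "Ovulation will be considered confirmed by a P4 level of" at least 3.0 ng/ml. The consequence of a second low value is final: "If ovulation is not confirmed at repeat Visit 2, the participant is not eligible to continue in the study". Sections 9.2 and 9.3 allow rescheduling to the next cycle for a yeast or urinary infection, and Section 9.3 also allows it after prohibited vaginal activity. Neither gives a next-cycle retest for a low P4. Visit 3 is to be "scheduled on or before day 24 (but not later than day 26) of the same menstrual cycle in which ovulation was confirmed", and Section 9.2 lets it fall on the same day as Visit 2 if the result is ready.

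**Treatment cycle: ovulation.** Under Section 9.6, Visit 6 follows a positive ovulation kit, takes place by Day 17 if the kit is still negative, and is partly repeated if the kit turns positive later. Section 9.7: "Visit 7 should occur 8-10 days after Visit 6 (or repeat Visit 6". Section 7.1 adds that later visits move if ovulation is late.

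**What is compared.** Tables 10 and 13 place the tissue immune-cell assessment, the explant test, the endometrial biopsy and endometrial thickness at Visits 3 and 7 only. Section 6.6.5 defines the explant endpoint as a comparison of the control and treatment cycles.

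**The concern.** The protocol foresees late ovulation and adapts to it in the treatment cycle, but not in the control cycle that supplies the tissue and ultrasound baseline. Two consequences follow for women at the long end of the eligible range.

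- An ovulatory woman may be tested before her P4 has had time to reach the threshold, and the protocol gives her no later test.
- If she passes, her baseline tissue is taken earlier in the luteal phase than her Visit 7 tissue. Part of her change from Visit 3 to Visit 7 is then cycle phase and not ring exposure.

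The measures concerned are the immune-cell markers (primary), and explant infectivity, endometrial histology and endometrial thickness (exploratory). Lavage markers, microflora and estradiol have their baseline at Visit 4 and are not part of this point.

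**Working it through.** **The plan's own timing (Table 4).** Insertion on cycle Day 7 is IVR Day 1, so Visit 6 on Day 14 is IVR Day 8, and Visit 7 at 14 + 8 to 14 + 10 is Day 22-24, or IVR Day 16-18. These figures reproduce. Visit 2 on Day 21 is shown at about IVR Day -14, which implies a cycle of 21 + 14 - 7 = 28 days. Visit 3 on Day 24 at about -10 implies 24 + 10 - 7 = 27 days. Table 4 therefore rests on a cycle of about 28 days.

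**Assumptions that the protocol does not give.** Luteal phase 14 days (range 12-16). P4 reaches 3 ng/ml 3 days after ovulation (range 2-4). Visit 7 at ovulation +8 to +10, or +7 to +9 if the kit turns positive one day before ovulation.

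**Formula.** For cycle length L, ovulation is on Day L - 14, and cycle day d lies d - (L - 14) days after it. Permitted Visit 3 days run from Day 20 (same day as an early Visit 2) to Day 26.

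| L | Ovulation day | Day 21 | Day 23 | Day 24 | Day 26 | Visit 3 days at +8 to +10 |
|---|---|---|---|---|---|---|
| 26 | 12 | +9 | +11 | +12 | +14 | 20-22 |
| 28 | 14 | +7 | +9 | +10 | +12 | 22-24 |
| 31 | 17 | +4 | +6 | +7 | +9 | 25-26 |
| 32 | 18 | +3 | +5 | +6 | +8 | 26 |
| 33 | 19 | +2 | +4 | +5 | +7 | none |
| 34 | 20 | +1 | +3 | +4 | +6 | none |
| 35 | 21 | 0 | +2 | +3 | +5 | none |

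**P4 test, nominal Day 23 repeat, 14-day luteal phase.** With a 2-day rise nobody fails. With 3 days, L = 35 fails. With 4 days, L = 34-35 fail. At a 3-day rise, a 12-day luteal phase extends failure to L = 33-35, and a 16-day luteal phase removes it. The repeat's own window also matters: drawn on Day 24, only L = 35 with a 4-day rise fails.

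**Baseline phase.** No permitted Visit 3 day matches Visit 7 for L = 33-35, or for L = 34-35 with the +7 to +9 anchor. The smallest possible gap is 8 - 7 = 1 day at L = 33 and 8 - 5 = 3 days at L = 35. At L = 35, Visit 7 falls on Day 29-31. With a 12-day luteal phase the lengths without a match are 31-35 (or 32-35). With 16 days, only L = 35 has no match on the first anchor; on the second, L = 35 can match and only L = 26 cannot.

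**The case against.** Several stronger readings are tempting, and the protocol does not support them.

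- **Long-cycle women are rejected.** A reader might infer this, but failure depends on luteal length and on how fast P4 rises. The protocol gives neither. On the central assumptions the risk is confined to 34-35 days, and some combinations exclude nobody.
- **The schedule suits only 28-31 days.** That describes nominal Day 24 alone. Visit 3 may be earlier, even on the day of Visit 2, so 26-27 day cycles can match. The Day 26 limit extends the match to 32 or 33 days.
- **Every Visit 7 is at a fixed luteal age.** If the kit never turns positive, Visit 6 stays calendar-set by Day 17 and Visit 7 follows from it. This is plausible in the levonorgestrel arm.
- **Phase differences would pass for ring effects between arms.** Visit 3 precedes randomization and follows one rule in all arms, and the comparisons in Section 14.3 are between arms, so the offset largely cancels. Some exposure remains: Section 14.6 relies on clinical review of descriptive change, about 50 x 1/5 = 10 completers are on placebo, and randomization is stratified by center only. For P4 itself an early baseline cannot create a false levonorgestrel effect, because every enrolled woman has a control-cycle value of at least 3 ng/ml.

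The two harms also overlap, since a woman who fails the P4 test supplies no baseline tissue. Nor is a narrower enrolled sample a validity flaw in a feasibility-sized, descriptive Phase I study. These points limit the concern to the long end of the range without removing it, because no use of the present windows aligns a 35-day cycle on the central assumptions.

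**Conclusion.** The point holds in a limited form. The eligible range and the control-cycle days do not fit together at the long end. Under a 14-day luteal phase, ovulatory women with 34-35 day cycles can be excluded without a later test, and those with cycles of about 33-35 days (34-35 on the later kit anchor) cannot have Visit 3 tissue in phase with Visit 7. The shortfall runs from about 1 day at 33 days to at least 3 days at 35 days, and to 5-7 days at 35 days if Visit 3 is on Day 24.

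The consequence is mainly for within-woman control-versus-treatment contrasts of Visit 3 and Visit 7 tissue and ultrasound, most directly the explant endpoint. The number of women affected cannot be computed, because no distribution of cycle length is given. The result rests on the assumed luteal length and P4 rise, with the ranges shown. The change is worth making because it costs little.

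**What to change.** In Sections 8.1, 9.2 and 9.3 and Tables 3 and 4, reconcile the control-cycle days with the eligible range by indexing them to reported cycle length L. Carry the change to the Synopsis and Section 7.1, which repeat Day 21.

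- Visit 2 at Day L-7 (+/-1)
- Repeat Visit 2 at Day L-5 (+/-1)
- Visit 3 on or before Day L-4 and not later than Day L-2

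At L = 28 this gives Days 21, 23, 24 and 26, exactly as now. At L = 26 it gives 19, 21, 22 and 24; at L = 35 it gives 28, 30, 31 and 33. With a 14-day luteal phase, the P4 draws fall at +7 and +9 and nominal Visit 3 at +10 for every L. With 12 or 16 days, nominal Visit 3 is at +8 or +12, again the same for every L. The interval from a repeat P4 to the last Visit 3 day stays at three days (26 - 23 now, and (L-2) - (L-5) after the change). Stating the rule in cycle days avoids a counting slip: in a 28-day cycle the next menses starts on Day 29, so seven days before it would be Day 22.

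The cost is amendment wording and a scheduling table for the sites, with no added visits, samples or participants. The rule relies on self-reported cycle length, already an eligibility item, and does not share Visit 7's kit anchor, so the phase match is approximate.

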### 9.3. Visit 3: Baseline Sample Collection

Once it has been confirmed that the participant meets all of the inclusion criteria and none of the exclusion criteria, baseline blood and genital tract samples will be taken at Visit 3. The visit should be scheduled on or before day 24 (but not later than day 26) of the same menstrual cycle in which ovulation was confirmed.

- An interval medical history will be collected.
- The study staff will ask the participant if she followed the instructions regarding vaginal products and vaginal activity. If she did not, she will be reminded of protocol requirements. Visit 2 and 3 may be rescheduled for her next menstrual cycle at the investigator's discretion.
- A directed physical exam, dipstick urinalysis (and possibly microscopy/cultures) and/or wet mount/pH will be performed, if indicated. If a symptomatic yeast or UTI infection is diagnosed, the participant will be treated and Visits 2 and 3 will be rescheduled for the next menstrual cycle. If symptomatic trichomoniasis or BV is diagnosed, the participant will be treated and discontinued.
- A urine specimen will be obtained for a urine pregnancy test.

If the participant meets all eligibility criteria and agrees to participate, she will continue in the study.

- A pelvic exam will be performed and the following procedures will be completed in the order listed. Findings will be managed as outlined in [Table 12: Safety Management Plan for Local Toxicity](#).
  - Transvaginal ultrasound to assess endometrial thickness.
  - Collection and processing of one endometrial biopsy (EVMS site only) for LNG PD as outlined in the study manual.
  - Collection and processing of cervicovaginal biopsies for safety (one at Profamilia and two at EVMS) and TFV PD (one biopsy at EVMS) as outlined in the study manual.
  - Applicable post-biopsy instructions will be discussed with the participant.
- A participant guidebook (which will include instructions regarding post-biopsy care, vaginal restrictions, and visit information) will be given to the participant to record any medications she takes or symptoms she experiences for the duration of the study, sexual and vaginal activity, removal/expulsion and reinsertion of study product, as well as menses and intermenstrual spotting. She will be instructed to bring the guidebook to every visit.
- The participant will be instructed to contact the site at any time during the study if she experiences:
  - Fever

- Moderate to severe urogenital symptoms (e.g., genital burning, irritation, stinging, pressure, rash, itching, discharge, odor, urgency, dysuria, or hematuria)
- Pelvic/lower abdominal pain
- Moderate to heavy intermenstrual bleeding (more than she would have during a normal period) or, during the week following a biopsy, any bleeding more than spotting

She will be asked to come in for an evaluation, if indicated.

- The participant will be reminded of the restrictions on vaginal activity (including intercourse) and product use as described at Visit 2.

Visit 4 will take place on day 7 (+/- 1 day) of one of the first two menstrual cycles after Visit 3, ideally in the first menstrual cycle.

